#### 2.13.1.
*Primary outcomes*.

Platelet aggregation rate, serum TLR4, MyD88, NF-*κ*B, COX-2, IL-6, CRP, TXB2 level as primary outcomes, which are tested at baseline, 14^th^ and 30^th^ day of treatment, will be analyzed with 2-way repeated measures Anova. A significant effect of group indicates that the platelet aggregation rate & TLR4/MyD88/NF-*κ*B signaling pathway associated proteins are different between groups after intervention.

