### 2.9. Primary outcomes

The primary outcome will be the change in platelet aggregation rate of elbow venous blood for platelet adhesion properties at baseline, 14^th^ day and 30^th^ day of treatment; Moreover, the serum TLR4, MyD88, NF-*κ*B, COX-2, IL-6, CRP, TXB2 level for AR improvement based on the TLR4/MyD88/NF-*κ*B signaling pathway would be also detected at above-mentioned 3 time points.

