### 2.11. Estimation of sample size

The study is powered for the primary outcome measure of platelet aggregation rate. The number of patients required for the study was computed a priori with software PASS 15.0.1, NCSS, LLC, America. The sample size calculation was based on the results of preliminary small sample pilot trial by our team, which showed a decrease of-14% in platelet aggregation rate in the exercise group compared with control group (autocorrelation coefficient 0.7, 3 time points). A 1-sided 0.05 level of significance and a sample size of 96 participants (48 per group) provided 80% statistical power to demonstrate this difference in platelet aggregation rate. To accommodate for a 10% attrition rate, we will recruit a total of 106 participants (53 per group) (PASS 15.0.1, 2-way repeated measures Anova; allocation ration = 1).

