### 2.13. Statistical analysis

Data analysis will be based on the full analysis set and per-protocol set in the light of data missingness (last-observation-carried-forward [LOCF] method) and robustness of our analytical results. All data will be analyzed using IBM SPSS Statistics 21.0 (v21.0, IBM Corp., Armonk, NY). Descriptive statistics will be performed with means ± standard deviations or median [interquartile range]. Baseline characteristics of patients will be summarized by groups and compared with Chi-square for categorical variables, and Student’s independent *t* test or nonparametric Mann-Whitney U test for the continuous variables. Primary and secondary outcomes are applicable to 2-way repeated measures Anova, and Post Hoc test will be for multiple comparisons between groups and time-points. If there is a violation of distribution assumption, appropriate transformation will be used. A *P* value < 2- sided 0.05 will be considered as significant.

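### Eight outcomes are declared primary and each is tested at two-sided 0.05 with no stated rule for success across them, while the trial is powered for only one

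*Protocol article*

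**What the plan says.** **Outcomes.** Section 2.9 of the protocol article opens in the singular: "The primary outcome will be the change in platelet aggregation rate of elbow venous blood". Under the same plural heading it then adds serum TLR4, MyD88, NF-κB, COX-2, IL-6, CRP and TXB2, measured at the same three time points. Section 2.13.1 leaves no doubt about their rank. It lists platelet aggregation rate and all seven markers and ends the list with "COX-2, IL-6, CRP, TXB2 level as primary outcomes". All are analysed by two-way repeated measures ANOVA.

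**Threshold and multiplicity.** Section 2.13 sets a single criterion: a P "value < 2- sided 0.05 will be considered as significant". The only multiplicity step it names is that a "Post Hoc test will be for multiple comparisons between groups and time-points". That step works within an outcome.

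**Reading of a result.** Section 2.13.1 begins its interpretation with "A significant effect of group indicates that the platelet aggregation rate" and goes on to say that this rate and the pathway proteins differ between groups. It does not say how many of the eight must be significant.

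**Sample size.** Section 2.11 states: "The study is powered for the primary outcome measure of platelet aggregation rate". It adds: "A 1-sided 0.05 level of significance and a sample size of 96 participants (48 per group) provided 80% statistical power". No calculation is given for any serum marker.

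**The concern.** A primary outcome fixes in advance what counts as success and carries the trial's error guarantee. Here eight outcomes hold that position, each has its own test at 0.05, and nothing says how the eight results combine into one conclusion. The sample size section treats one of the eight as the basis of the design; the analysis section treats all eight alike.

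The trial's stated aim is to support the study herb as a partial substitute for aspirin in aspirin-resistant patients. As the plan stands, nothing would prevent a significant CRP or IL-6 result beside a null platelet aggregation result from being presented as a positive primary finding. The 5% level would not hold for such a claim, and the power statement would not describe it.

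**Working it through.** **Inputs.** Number of primary outcomes: 8 (Section 2.13.1). Level of each test: two-sided 0.05 (Section 2.13). Adjustment across outcomes: none stated. Design figures: 48 per group, one-sided 0.05, 80% power, platelet aggregation rate only (Section 2.11). Correlation between outcomes: not given. The 0.7 in Section 2.11 is the correlation over time within one outcome and cannot be used here.

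**The plan's own figure.** The document states no family-wise error rate, so there is none to reproduce. The sample size of 96 cannot be recomputed either, because Section 2.11 gives a 14% decrease without a standard deviation. The step to 106 agrees with 96 × 1.10 = 105.6; dividing by 0.90 gives 106.7, a difference of one patient that does not matter here.

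**Step 1: any one of eight suffices, independent outcomes.** Under the global null, the chance of at least one false positive in either direction is 1 − 0.95^8 = 0.337. For false positives favouring the study herb, each test has level 0.025, so 1 − 0.975^8 = 0.183.

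**Step 2: the same with correlated outcomes.** For eight normal test statistics with common correlation ρ and c = 1.96, the two-directional rate is

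1 − ∫ φ(x) [Φ((c − √ρ·x)/√(1−ρ)) − Φ((−c − √ρ·x)/√(1−ρ))]^8 dx.

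For the benefit direction only, the second Φ term is dropped.

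| Assumed ρ | Either direction | Benefit only |
|---|---|---|
| 0 | 33.7% | 18.3% |
| 0.3 | 30.0% | 15.2% |
| 0.5 | 25.0% | 12.5% |
| 0.7 | 19.1% | 9.5% |
| 0.8 | 15.8% | 7.9% |
| 0.9 | 11.9% | not computed |

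The nominal values are 5% and 2.5%. These figures count one group test per outcome. Section 2.3.1 uses two inducers for platelet aggregation; if both were analysed there would be nine tests, and the independent figure would be 1 − 0.95^9 = 37.0%.

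**Step 3: all eight must succeed.** The error for that joint claim is then at most 5%, but power falls. If each test had 80% power and the tests were independent, joint power would be 0.8^8 = 0.168. Positive correlation raises this, but the 80% in Section 2.11 still describes one outcome and not the joint claim.

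**Step 4: would a simple Bonferroni split fit this sample size?** The per-test level would be 0.05/8 = 0.00625, and the family-wise error 4.9% (independent) or 4.0% (ρ = 0.5). The standardised difference implied by 48 per group at one-sided 0.05 and 80% power is (1.645 + 0.842) × √(2/48) = 0.508. With that difference:

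- Power at two-sided 0.05 is Φ(2.487 − 1.960) = 0.70.
- Power at two-sided 0.00625 is Φ(2.487 − 2.734) = 0.40.
- About 100 per group would be needed to restore 80%.

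The starting value is 70% and not 80% because Section 2.11 is one-sided and Section 2.13 two-sided, which is a separate matter. An equal split over eight therefore fits this trial poorly.

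**The case against.** **The error range is assumed.** This stands. The eight measures are presented as parts of one linked pathway, so independence is the least plausible end of the range. A reader might take some 20% to 34% as the established false-positive rate. The documents do not support that: they give no correlations, and strong correlation brings the figure down to 12%. The conclusion survives, since 12% is still more than twice the nominal 5%.

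**The rate counts both directions.** This also stands. A false claim of benefit needs significance in the favourable direction, and for that the figures are about half as large, to be compared with 2.5%.

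**The success rule is inferred.** A reader might infer that the plan lets any one significant marker establish success. The text does not say so, nor does it say that all must succeed. The defect is that no rule is stated, and Steps 1 and 2 apply only under the first reading.

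**Section 2.9 does not simply contradict Section 2.13.1.** Its first clause is singular, but its heading is plural and it lists the same seven markers. The primary objective in the Introduction covers both efficacy and mechanism, so the markers' rank may be deliberate. The real mismatch is with Section 2.11.

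**Multiplicity is often left to the SAP.** This is fair as far as the choice of method goes, and the article cannot show that no adjustment will be made. But the article itself fixes eight primaries, the threshold and a power basis for one; an SAP that demoted seven of them would contradict Section 2.13.1.

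**Conclusion.** The point holds. The protocol article names eight primary outcomes, applies one two-sided 0.05 threshold without a decision rule, testing order or adjustment across them, and powers the trial for one.

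Its size depends on the reading. If any one outcome suffices, the family-wise error in either direction is 34% for independent outcomes and 12% at a correlation of 0.9, with 25% and 19% at 0.5 and 0.7; the correlations are assumed. In the benefit direction it is about 18% to 10% for correlations from 0 to 0.7. If all eight must succeed, the error is controlled and the 80% power claim fails to apply. Either way the text needs correction, because it leaves the definition of success open.

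One further inference should be avoided: the registry record is not among the documents, so nothing can be said about whether it carries the same problem.

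**What to change.** In Sections 2.9 and 2.13.1, make platelet aggregation rate the sole primary outcome, as Section 2.11 already assumes. Move TLR4, MyD88, NF-κB, COX-2, IL-6, CRP and TXB2 to secondary (mechanism) outcomes. Test these seven as one family with Holm adjustment, and only if the primary outcome is significant; otherwise report them as exploratory, with estimates and confidence intervals. Check the registry entry and align it if needed. Make the change before any outcome data are compared by group.

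Other schemes, such as a fixed testing order, an alpha split or explicit co-primaries, would also be valid if stated. The single primary is preferred because it keeps the existing power basis and needs no more patients on this account.

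The cost is wording in two sections, and single-marker results lose primary status and face a stricter threshold. Section 2.2 requires modifications that may affect the conduct of the trial to go to the ethics committee, so the change may need to be submitted there.

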## 2. Methods/design

### 2.1. Study design

This is a prospective 2-center, assessor and statistician blinded, randomized, controlled trial with a parallel 2-arm group from June 2021 to May 2023. This study protocol is draw up based on Recommendations for Interventional Trials (SPIRIT) 2013 statement.^[10]^ The SPIRIT checklist will be presented in (Table S1, Supplemental Digital Content, http://links.lww.com/MD/H991). A total of 106 participants will be randomized into 2 groups at a ratio of 1:1. Participants in the treatment group will be treated with conventional treatments plus *Panax notoginseng (Sanqi*). Participants in the control group will be treated with conventional treatments.

The whole study period is 35 days, including 5-days baseline observation, 30-days treatment. Subjects will be measured with the platelet aggregation rate and serum TLR4, MyD88, NF-*κ*B, COX-2, IL-6, CRP, TXB2 level for clinical efficacy and mechanisms at baseline and the 14^th^, 30^th^ day of treatment. (Fig. 1, Table 1).

**Table 1 T1:** Schedule of enrollment, interventions and assessments.

Study procedure	Study period		
	Enrollment（d）	treatment period （d）	
Timepoints	-5^th^-0d	14^th^d ± 1d	30^th^d ± 1d
Enrolment			
Demographics	X		
Vital signs	X		
Medical history	X		
Complications	X		
Eligibility screen	X		
PHQ-9	X		
GAD-7	X		
MMSE	X		
Informed consent	X		
Random allocation	X		
Interventions			
Conventional treatments + Panax notoginseng		X	X
Conventional treatments		X	X
Assessments			
Platelet aggregation rate	X	X	X
TLR4, MyD88, NF-*κ*B, COX-2, IL-6, CRP, TXB2	X	X	X
Coagulation function	X	X	X
Safety evaluations	X	X	X
Patient compliance	X		
Drug combinations	X		
Adverse events	X		
Research summary	X		
Review statements	X		

GAD = generalized anxiety disorder, MMSE = mini-mental state examination, PHQ = patient health questionnaire.

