#### 2.13.2.
*Secondary outcomes*.

Coagulation tested at above-mentioned 3 time points, will be also analyzed with 2-way repeated measures Anova.

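### Section 2.13.1 reads the treatment effect from a group main effect that averages in the pre-treatment baseline, so the effect is diluted by a third and mislabelled as a post-treatment difference

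*Protocol article*

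**What the plan says.** Section 2.9 defines the endpoint as a change: "The primary outcome will be the change in platelet aggregation rate of elbow venous blood", measured at baseline, day 14 and day 30. Section 2.1 shows that baseline precedes treatment: "The whole study period is 35 days, including 5-days baseline observation, 30-days treatment".

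Section 2.13.1 says of platelet aggregation and the seven serum markers: "which are tested at baseline, 14^th^ and 30^th^ day of treatment, will be analyzed with 2-way repeated measures Anova". It then says how the result will be read: "A significant effect of group indicates that the platelet aggregation rate" and the "signaling pathway associated proteins are different between groups after intervention". This is the only rule the article gives for drawing a primary conclusion. Neither a group-by-time interaction nor a baseline covariate is named anywhere. Section 2.13 adds only that "Post Hoc test will be for multiple comparisons between groups and time-points".

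Section 2.11 bases the sample size on a 14% reduction from a pilot ("autocorrelation coefficient 0.7, 3 time points") and a two-way repeated measures ANOVA, with 48 per group for 80% power at 1-sided 0.05. It does not say which ANOVA term was powered.

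**The concern.** A group main effect in a repeated measures ANOVA compares the arms on each patient's average over all time levels. One of the three levels here was measured before any treatment, when randomised arms have no expected difference. The quantity tested is therefore not the difference after intervention that section 2.13.1 says it is, nor the change that section 2.9 sets as the outcome.

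There are three consequences. The estimate is pulled towards zero. Any chance baseline difference between the arms enters the comparison directly. The strong within-patient correlation, which could sharpen the comparison if baseline were adjusted for, is not used. A real effect could be missed, and the published size of the effect would be understated, for every outcome read under this rule.

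**Working it through.** **Dilution (needs no SD).** Let d14 and d30 be the true group differences at the two post-treatment visits. The expected baseline difference is 0 under randomisation, so

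group main effect = (0 + d14 + d30)/3 = (2/3) × (d14 + d30)/2.

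That is two-thirds of the mean post-treatment difference for any profile. Relative to day 30 alone, the factor is 0.67 if the effects are equal and (14/30 + 1)/3 = 0.49 if the effect grows linearly from day 0.

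**The plan's own figure.** The 96 patients cannot be reproduced, because section 2.11 gives no SD and does not say whether 14% is absolute or relative, or at which time. I therefore solved for the standardised difference that makes 48 per group give 80% power at 1-sided 0.05 for the mean of three times (noncentral t, 94 df).

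- Compound symmetry, rho 0.7: variance of the mean = (1 + 2 × 0.7)/3 = 0.80 σ². Difference 0.457 SD; noncentrality 0.457/√(0.80 × 2/48) = 2.50.
- AR(1), 0.7: variance of the mean 0.753 σ². Difference 0.444 SD; noncentrality 2.50.

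**Power if that difference is a post-treatment effect, equal at days 14 and 30.**

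- Group main effect: noncentrality (2/3) × 2.50 = 1.67 under either structure.
- Baseline-adjusted mean of days 14 and 30, compound symmetry: residual variance 0.85 − 0.70² = 0.36 σ²; noncentrality 0.457/√(0.36 × 2/48) = 3.73.
- The same under AR(1): 0.85 − 0.595² = 0.496 σ²; noncentrality 0.444/√(0.496 × 2/48) = 3.09.

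| Test, 48 per group | 1-sided 0.05 | 2-sided 0.05 |
|---|---|---|
| Group effect, no dilution (as back-solved) | 80% | 70% |
| Group effect, baseline included | 51% | 38% |
| Baseline-adjusted, compound symmetry | 98% | 96% |
| Baseline-adjusted, AR(1) | 92% | 86% |

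The group-by-time F test at 0.05 has 85% power (compound symmetry) or 71% (AR(1)). To regain 80% power the diluted group effect would need about 107 per arm (1-sided) or 136 per arm (2-sided); the plan recruits 53.

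**Sensitivity to the unstated SD**, if 14% means 14 points at both post-treatment visits (compound symmetry, 2-sided 0.05):

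| SD (points) | Group effect | Baseline-adjusted |
|---|---|---|
| 15 | 92% | >99% |
| 20 | 72% | >99% |
| 25 | 53% | 99% |
| 30 | 39% | 97% |
| 35 | 30% | 90% |

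**Type I error.** In 20,000 simulated trials with no treatment effect, the group-effect test rejected in 5.0% at 2-sided 0.05.

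**Conditional on a chance baseline imbalance of z standard errors** (compound symmetry, no effect, normal approximation): the group-effect statistic has mean 0.80z/√0.80 and SD √((0.80 − 0.80²)/0.80) = 0.447. At z = 1, 1.5 and 2 it exceeds 1.96 with probability 0.9%, 8% and 35%. An imbalance of 2 SE or more occurs in about 4.6% of trials.

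**The case against.** The strongest defence is that the stated test is not invalid. Under randomisation the baseline contributes nothing in expectation, so a significant group effect is evidence of a treatment effect at the nominal error rate. This stands. A reader might infer that the rule inflates false positives, or tests nothing about treatment, and the article supports neither. The 35% figure is conditional on an uncommon imbalance, and any comparison that ignores baseline has some dependence of this kind.

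The fall from 80% to 38% should not be put down to the group effect alone. Section 2.11 uses a 1-sided level and section 2.13 a 2-sided one, which is a separate conflict. Sidedness alone takes 80% to 70%; dilution alone takes it to 51%.

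A reader might also infer that section 2.11 makes the same error by counting three time points. It does not say which term or time point was powered, and a group-by-time calculation would count baseline too. Nor does section 2.13.2 state the faulty rule: coagulation "will be also analyzed with 2-way repeated measures Anova", with no group effect named.

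The post hoc comparisons in section 2.13 could supply group contrasts at days 14 and 30. They are unspecified, however, and section 2.13.1 does not rest the primary conclusion on them. An analysis plan not shown here may give more model detail, but one based on the interaction would contradict the sentence in 2.13.1.

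**Conclusion.** The concern holds for the sentence in section 2.13.1. As written, the primary conclusion is drawn from a quantity that averages in the pre-treatment value, is labelled as a difference after intervention, and does not match the change outcome of section 2.9. The loss of one third of the mean post-treatment difference is exact in expectation and needs no assumption beyond randomisation.

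The cost in power is conditional. It rests on rho 0.7, 48 per group, an effect back-solved from the plan's own 80% power, and the 14% being a post-treatment difference present at both visits. On those terms the group effect has roughly half the intended chance of success at the 2-sided level, where a baseline-adjusted comparison would have ample power. With a small SD the group effect could still be adequately powered. If the 14% already describes the average over three times, dilution leaves the planned power intact, but the mismatch with the outcome and the mislabelling remain.

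**What to change.** - **Section 2.13.1:** replace the sentence on the group effect with one pre-stated treatment contrast on the post-treatment values, with baseline as covariate, either at day 30 or for the mean of days 14 and 30. At minimum, keep the ANOVA and rest the decision on the group-by-time interaction.
- **Section 2.11:** say which contrast and time point the 14% refers to, whether it is absolute or relative, and the SD used. Restate the power for the chosen test.
- **Section 2.13.2:** use the same contrast for coagulation, for consistency.

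The cost is analysis wording and a rerun power statement. Baseline is already measured, so no new visits or data are needed.

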#### 2.13.2.
*Secondary outcomes*.

Coagulation tested at above-mentioned 3 time points, will be also analyzed with 2-way repeated measures Anova.

#### 2.13.3.
*Safety evaluation*.

The number (n) and percentage (%) of participants with AEs recorded in the diary will be calculated and compared using Chi-square test.

### 2.14.
*Quality control*

Reasons of dropouts during research periods will be fully recorded for data analysis. To ensure quality, the PI ([name]) and sub-PI ([name]) will verify all study process every 2 months and check data authenticity every 2 week on-site or online. Moreover, a third party, scientific research department of *Xi’an Hospital of Traditional Chinese Medicine (Xi’an Affiliated Hospital of Shaanxi Provincial Hospital of Chinese Medicine*), will be invited to manage the data independently.

Since this study mainly involves some objective indicators tested by device, measurement bias are mainly from different devices. In order to increase consistency, on the 1 hand, blood samples will be taken from patients at fixed time (7:30 am) by a fixed nurse. On the other hand, blood samples from the sub-center (*Shanxi Provincial Hospital of Chinese Medicine [Shaanxi Academy of Traditional Chinese Medicine]*) will be delivered to our hospital(*Xi’an Hospital of Traditional Chinese Medicine [Xi’an Affiliated Hospital of Shaanxi Provincial Hospital of Chinese Medicine]*) on the day for unified storage and detection. Moreover, record cards for all patients will be prepared for treatment history, including treatment date, personal information and their signatures.

## 3. Discussion

The occurrence of AR does increase the recurrence risk of cerebrovascular events. Due to the complexity of its pathogenesis, there is still no consensus on its treatment.

Therefore, we hope to obtain an appropriate partial substitute of aspirin for AR individuals through the advantages of multi-target and multi-pathway of TCM. From the perspective, anti-platelet aggregation drugs belong to the category of activating blood and removing stasis herbs medicine in TCM.^[21]^ So, activating blood and removing stasis herbs medicine may reduce the incidence and recurrence of stroke.

Herb medicine *sanqi* is the dried roots and rhizomes of Panax notoginseng. In clinic, it is mainly used for the treatment of diseases of cardio-cerebral system and vascular system.^[22]^ Modern pharmacological studies suggest that *Panax notoginseng (Sanqi*) can improve brain circulation and protect brain tissue. *Panax notoginseng (Sanqi*) powder can be used for cerebral infarction by the effect of activating blood and removing stasis.^[23]^ Its main active components, total saponins of *Panax notoginseng (Sanqi*), can effectively reduce blood lipid - glucose content, dilate blood vessels, decompose and inhibit the small thrombi in vessels with the enzyme- promoted cascade reaction, which has a certain effect on stroke.^[22]^

A great deal of experimental evidence indicates that inflammatory injury exerts a significant impact on the development of cerebral ischemia.^[24]^ During cerebral ischemia, TNF-*α*,IL-1,IL-6, et cetera, involved in inflammation, which would cause irreversible damage to brain. NF-*κ*B plays an important role in the inflammation. Phosphorylation of I*κ*B leads to phosphorylation of NF-*κ*B, which initiates transcription, regulates expression of cellular inflammatory factors, and promotes inflammation. In addition, inflammatory factors and adhesion molecules can induce further NF-*κ*B activation and aggravate the inflammatory process.^[25]^ Studies have shown that total saponins of *Panax notoginseng (Sanqi*) can inhibit the NF-*κ*B activation, block the I*κ*B phosphorylation, reduce the NF-*κ*B transcription into the nucleus, inhibit the expression of TNF-*α* in ischemic brain tissue.^[26]^ TLR4, a member of the signal transduction family, binded to the adaptor protein MyD88 and interleukin-related kinases to activate the TLR4/MyD88/NF-*κ*B signaling pathway could induce inflammatory responses.^[27]^ Study shows that it may ameliorate cerebral ischemia injury by decreasing expression of TLR4, MyD88 and NF-*κ*B P65 protein via inhibiting the TLR4/MyD88/NF-*κ*B P65 signaling pathway.^[28]^ Therefore, the possible mechanism of *Panax notoginseng (Sanqi*) for AR in stroke may be by inhibiting the inflammatory TLR4/MyD88/NF-*κ*B pathway.

Our study protocol exists several limits, such as open-blinding, short observation time, and without dose-effect relationship. However, we will try our best to attempt to minimize the biases that may influence study results. Finally we intend to demonstrate the hypothesis that *Panax notoginseng (Sanqi*) as an alternative may be an appropriate partial substitute of aspirin for AR individuals via TLR4/MyD88/NF-*κ*B signaling pathway.
